### Research aims

This project seeks to expand our existing work by conducting a multi-site randomised placebo-controlled trial of NAC in the treatment of clozapine-resistant SZ, with 8, 24 and 52 week assessments. We will target negative symptoms (primary outcome), quality of life and cognition (secondary outcomes). An additional novel aspect of this proposed study is the examination of both peripheral and cortical GSH concentrations, the latter in a subset of patients using MRS. This will be the first study using NAC to target drug resistant clozapine treated SZ patients specifically; and the first to conduct a 52-week outcome study of the efficacy of NAC in SZ. It is hypothesised that NAC will be superior to placebo in the treatment of negative symptoms in SZ patients currently taking clozapine. Additional benefits are predicted in their quality of life and cognitive functioning. Further analysis of peripheral and cortical GSH concentrations is expected to show increases, whereby increases in cortical GSH will increase cortical functioning.

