### Magnetic Resonance Spectroscopy (MRS): Cortical glutathione

A sub-set of participants (*N* = 42) will be invited to undergo MRI scans. Scans will be acquired using Swinburne University’s (Melbourne) Siemens Trio 3 Tesla MRI (Siemens AG, Munich, Germany). Participants will spend 1 hour in the scanner. An MRS sequence enables the measurement of levels of metabolites found in the brain. The cerebral metabolites that will be measured in the current study are creatine (Cre) and GSH. MRS voxels will be prescribed in the medial prefrontal cortex (mPFC) and will be 50 × 30 × 30 mm. The voxel will be positioned using an axial T1-weighted gradient-echo image. Spectral processing with be performed using *LCModel* software which permits us to calculate GSH concentrations (calculated in reference to total Cre).

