### Statistical analyses

Data will be analysed using R 3.1.2 (R Foundation for Statistical Computing, Vienna, Austria and SPSS where relevant). Intention-to-treat analyses will be employed to prevent over-estimation of efficacy. Categorical variables will be analysed using chi-squared tests (or Fisher’s exact test for small samples). A mixed-effects model, repeated measures (MMRM) approach will be used to examine the longitudinal profile of all continuous variables at weeks 8, 24, and 52 post-baseline. For all MMRM analyses, baseline scores will be used as covariates and the models will include pre-specified fixed effects of treatment, site, and time, and treatment-by-time and treatment-by-site interactions.

The MMRM modelling for the primary outcome measure – PANSS negative scores and CAINS scores – will also include baseline PANSS Positive, Negative, and General Psychopathology scores, as covariates. The secondary outcomes consist of MANSA, AQoL and MCCB global score, while the process outcomes include GSH concentrations peripherally and cortically, respectively.

Secondary analyses using Analysis of Covariance will be conducted to compare change scores during treatment and follow-up phases for all primary, secondary, and process outcomes using treatment group as a main effect with the baseline score as a covariate. Site will not be included in the analysis for the MRS data, but will be for the peripheral data. Correlational analyses will also be performed to examine for relationships between outcome variables (i.e., treatment response with cognition and GSH levels, peripherally and cortically).

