## Discussion

SZ is one of the most disabling chronic diseases for people aged 18–45 years, and impacts multiple domains of functioning as well as increasing mortality risks. Current treatments remain suboptimal for many patients, with residual negative and cognitive symptoms being particularly disabling. Improvements and advances in the intervention options for treatment-resistant psychosis are in great demand. Whilst clozapine has profound benefits for some individuals who do not respond to other antipsychotics, it is not as effective for many others. This large scale clinical trial will investigate the efficacy of NAC as a possible adjunctive medication to clozapine. In addition, this trial will run for 52 weeks providing the longest follow up examination of the impact of NAC on SZ to date. This trial, if successful, will establish a cheap, safe and easy-to-use agent (NAC) as a ‘go to’ adjunct in patients only partly responsive to clozapine. This work will provide crucial information regarding the clinical value of this treatment approach. Given the personal and societal cost of treatment resistant psychosis, the research will therefore have great importance for this mental health condition. In addition, we will be able to assess in detail the effects of this agent on cognitive functioning as well as investigating in some detail the glutathione hypothesis of SZ, by examining peripheral and cortical markers of glutamatergic activity.

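### The correlations linking GSH to response and cognition state no adjustment for treatment arm; pooled across arms, they can show a link that treatment alone creates

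*Protocol article*

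**What the plan says.** Research aims words the mechanism causally for cortical GSH: "Further analysis of peripheral and cortical GSH concentrations is expected to show increases, whereby increases in cortical GSH will increase cortical functioning".

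Statistical analyses classes GSH as a process outcome: "the process outcomes include GSH concentrations peripherally and cortically, respectively". It gives GSH two between-arm analyses:

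- The mixed model for repeated measures (MMRM) "approach will be used to examine the longitudinal profile of all continuous variables at weeks 8, 24, and 52 post-baseline", with treatment and treatment-by-time among its fixed effects.
- An analysis of covariance "for all primary, secondary, and process outcomes using treatment group as a main effect with the baseline score as a covariate".

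The relation between GSH and the other outcomes is covered by a single further sentence: "Correlational analyses will also be performed to examine for relationships between outcome variables (i.e., treatment response with cognition and GSH levels", for peripheral and for cortical GSH. No model terms are listed for it.

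On measurement, the MRS section states: "The cerebral metabolites that will be measured in the current study are creatine (Cre) and GSH". The blood panel consists of thiols and their disulphides, given as an open list of examples. Cognition is assessed with MATRICS and the WASI at all four visits (Table 1). The Discussion says the glutathione hypothesis will be investigated "by examining peripheral and cortical markers of glutamatergic activity".

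**The concern.** The trial expects NAC to raise GSH, reduce negative symptoms and improve cognition. Two variables that randomised treatment moves in the favourable direction will correlate across the whole sample, because one arm sits higher on both. That happens even if, within each arm, patients with larger GSH rises do no better than the rest. A pooled correlation therefore cannot separate GSH carrying the benefit from NAC doing two unrelated things.

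At stake is how the mechanistic result is read. This is the only analysis that bears on the causal statement in Research aims, and when NAC moves both variables favourably the bias runs towards the hypothesis. No primary, secondary or between-arm process result is affected.

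**Working it through.** **Inputs from the article**

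- Effect on negative symptoms: d = 0.5 (sample-size paragraph).
- Allocation 1:1 (Randomisation and blinding).
- Sample sizes: 168 × 0.80 ≈ 134 after the 20% dropout by week 8; 2 × 45 = 90, the number the power calculation requires; 36 MRS patients at weeks 8 and 52.
- The only alpha stated is the study-wide 0.01, two-tailed, in the power calculation. None is set for the correlations.

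**Assumptions**

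- GSH shift from NAC of 0.5, 1, 2 or 3 within-arm SD. The article gives no figure.
- Nominal two-sided 0.05 for the correlations, with 0.01 as a check.
- d = 0.5 also stands in for cognition, for which no effect size is stated.
- Within-arm correlation of zero, so any significant result is a false link. Improvement is scored as positive.

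The article gives no figure for these correlations, so there is nothing to reproduce first.

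**Step 1. Induced correlation.** With equal arms, treatment adds d²/4 to each variance (within-arm variance 1) and d_G·d_Y/4 to the covariance:

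r = (d_G·d_Y/4) / √[(1 + d_G²/4)(1 + d_Y²/4)]

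With d_Y = 0.5:

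- d_G = 0.5: 0.0625 / 1.0625 = 0.06
- d_G = 1: 0.125 / √(1.25 × 1.0625) = 0.11
- d_G = 2: 0.25 / √(2 × 1.0625) = 0.17
- d_G = 3: 0.375 / √(3.25 × 1.0625) = 0.20

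**Step 2. Chance of a significant pooled correlation.** By Fisher's z, for d_G = 2 and n = 134: atanh(0.1715) × √131 = 1.98, and P(Z > 1.96 − 1.98) ≈ 0.51. A simulation of 40,000 trials per cell gave 52% for that cell and agreed closely elsewhere. The simulated rates are:

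| GSH shift (SD) | pooled r | n = 36 | n = 90 | n = 134 |
|---|---|---|---|---|
| 0.5 | 0.06 | 6% | 9% | 10% |
| 1 | 0.11 | 10% | 18% | 24% |
| 2 | 0.17 | 17% | 37% | 52% |
| 3 | 0.20 | 22% | 49% | 66% |

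**Step 3. Same data, adjusted for arm.** The partial correlation given arm rejected in about 5% of trials in every cell.

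**Step 4. At alpha 0.01.** Over the same range of shifts, the pooled rates fall to 1–8% (n = 36), 2–25% (n = 90) and 3–41% (n = 134). The arm-adjusted rate is about 1%.

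**Step 5. Measures against claims.** The MRS section lists creatine and GSH. The blood section lists thiols and disulphides. Neither names glutamate, yet the Discussion describes these as glutamatergic markers. No measure is labelled cortical functioning; the nearest is cognition, chiefly MATRICS.

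**The case against.** The strongest reply is that the article does not say the correlations are pooled or unadjusted. A within-arm partial correlation is also a correlational analysis and would fit the sentence as written. This is a condensed article, and the conditioning of exploratory analyses may sit in a plan that is not shown. That stands: unadjusted is an inference from silence. It is a natural one, because the same section names the treatment term for the MMRM and the covariance analysis and says where site enters, but names nothing for the correlations.

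The sizes are also open to challenge. The upper rates need a GSH shift of 3 SD, and only two of the twelve cells at alpha 0.05 exceed 50%. The causal wording concerns cortical GSH, which is measured only in the imaging subset, where the rate is at most about 22%. Spurious correlations of 0.06 to 0.20 explain roughly 0.3% to 4% of variance. All of this stands, and it limits the size of the problem but not its direction.

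A reader might infer three stronger points that the article does not support:

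- *The whole mechanism is tested by correlation.* It is not; whether NAC raises GSH is tested between randomised arms.
- *The trial claims a mediation test of GSH on symptoms.* It does not. GSH is a process outcome, the worded causal link is to cortical functioning only, and no decision rule depends on it.
- *Cortical functioning is not measured at all.* Cognition is a reasonable behavioural proxy; the gap is that the article does not name it as the measure meant.

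**Conclusion.** The point holds in a limited form. The randomised test of NAC on GSH is sound. The step from GSH to response and cognition rests on correlations between post-randomisation outcomes with no conditioning on arm stated. If they are run across pooled arms and NAC moves both variables, false links occur at the rates tabulated above: slight for a small GSH shift, substantial for a large shift in peripheral GSH across the full sample, and modest in the MRS subset. The direction needs only that NAC shifts both variables favourably; the size rests on the assumed GSH shift and alpha, and on d = 0.5 applying to the outcome concerned.

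The rates do not show that the trial would probably report false support for the glutathione hypothesis; that would require a shift of about 2 SD or more together with the larger sample. Nor does arm adjustment establish mechanism, since confounding between GSH and outcome within arms remains.

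The glutamatergic phrase is a wording mismatch between the Discussion and the listed measures. It affects no stated aim, outcome or analysis.

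**What to change.** Under Statistical analyses, state that the GSH–response and GSH–cognition associations will be adjusted for treatment arm: regress change in outcome on change in GSH, with arm and both baselines in the model, or report pooled within-arm partial correlations. Add that the results will be interpreted as associations, not as proof of mediation. If an analysis plan already does this, one clarifying clause is enough.

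Under Research aims, replace "increases in cortical GSH will increase cortical functioning" with wording that names the MATRICS global score as the measure meant. In the Discussion, reconcile "by examining peripheral and cortical markers of glutamatergic activity" with the measures listed: delete the phrase, or add glutamate to the reported metabolites if the acquired spectra support it.

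The cost is wording and a few model terms, with no new visits, scans or patients. In the MRS subset the regression has five coefficients (intercept, GSH change, arm, two baselines), leaving 36 − 5 = 31 residual degrees of freedom. The drawback is less spread in GSH: at a 2 SD shift the within-arm variance is half the pooled variance (1 against 1 + 2²/4 = 2), so fewer associations will reach significance.

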### Data monitoring

A Data Safety Monitoring Board (DSMB) will oversee the conduct of the current trial. This board includes four experts external to the trial team.

## Discussion

SZ is one of the most disabling chronic diseases for people aged 18–45 years, and impacts multiple domains of functioning as well as increasing mortality risks. Current treatments remain suboptimal for many patients, with residual negative and cognitive symptoms being particularly disabling. Improvements and advances in the intervention options for treatment-resistant psychosis are in great demand. Whilst clozapine has profound benefits for some individuals who do not respond to other antipsychotics, it is not as effective for many others. This large scale clinical trial will investigate the efficacy of NAC as a possible adjunctive medication to clozapine. In addition, this trial will run for 52 weeks providing the longest follow up examination of the impact of NAC on SZ to date. This trial, if successful, will establish a cheap, safe and easy-to-use agent (NAC) as a ‘go to’ adjunct in patients only partly responsive to clozapine. This work will provide crucial information regarding the clinical value of this treatment approach. Given the personal and societal cost of treatment resistant psychosis, the research will therefore have great importance for this mental health condition. In addition, we will be able to assess in detail the effects of this agent on cognitive functioning as well as investigating in some detail the glutathione hypothesis of SZ, by examining peripheral and cortical markers of glutamatergic activity.

### Trial status

Patient recruitment was about to commence at the time of manuscript submission. Data collection will continue until at least June 2019.

Australian and New Zealand Clinical Trials Registration Number (TRN) ACTRN12615001273572 https://www.anzctr.org.au/Trial/Registration/TrialReview.aspx?id=369601.

## Abbreviations

AQoL: Assessment of Quality of Life
CAINS: Clinical Assessment Interview for Negative Symptoms
GSH: Glutathione
MANSA: Manchester Quality of Life Scale
MMRM: Mixed-effects model, repeated measures
MRS: Proton magnetic spectroscopy
NAC: *N*-Acetylcysteine
PANSS: Positive and Negative Syndrome Scale
QoL: Quality of life
SHIP: Survey of High Impact Psychosis
SZ: Schizophrenia.
